#### Tolerability

All randomised participants who receive at least one dose of intervention or control treatment will be included in the planned analyses. Comparison of the frequency of treatment withdrawal between the intervention and the control group will be tested using Chi-square statistics. The numbers of participants discontinuing treatment prematurely for any reason will be summarised by treatment group and by reasons for discontinuation. The incidence of all suspected serious adverse treatment reactions will be summarised by treatment group.

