### Blinding

Due to the nature of the intervention only single blinding (of researchers, not of participants) is possible. Members of the trial steering committee, management committee, and other study team members (with the exception of the project co-ordinator and the Quitline senior research manager) will remain blinded to treatment allocation until the code is broken (namely, after the last follow-up call is completed and the data recorded). The project co-ordinator will not be blinded as they will be responsible for distributing the cytisine to participants. The senior research manager and research assistants based at Quitline will not be blinded to treatment allocation, as they are required to know which group each participant has been allocated to in order to conduct the scheduled follow-up calls.

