#### Secondary outcome

The following secondary outcome measures will be assessed at one week and one month after the Quit date in the treatment group only:

• *Information related to the use of cytisine: *Participants will be asked for their views on the use of cytisine as a cessation aid (i.e. whether they would recommend the treatment to another smoker and whether they liked or disliked using the product).

• *Participants' treatment compliance: *Self-reported pill counts (also asked at two months), concomitant cytisine and NRT use (also asked at two months), early stopping of cytisine and reasons why.

The following secondary outcome measures will be assessed in all participants at one week and one, two and six months after the Quit date:

• *The physical signs and symptoms associated with withdrawal: *Assessed using the MPSS [27] in abstinent smokers, measured at one week, one month and two months only.

• *Self-rated chances of quitting: *Measured at one week, one month and two months only.

• *Seven-day point prevalence: *The proportion of participants that have stopped smoking, defined as self-report of having smoked no cigarettes (not even a puff) in the past seven days. Measured at every time point.

• *Continuous abstinence: *The proportion of participants that have stopped smoking, defined as self-report of smoking not more than five cigarettes from the Quit date. Assessed at every time point.

• *Use of cigarettes: *If the participant is smoking at any time point, the following outcomes will be assessed: number of cigarettes smoked per day; proportion of participants who have significantly reduced their daily smoking level (defined as reducing consumption by at least 25% in terms of numbers of cigarettes per day or weight of loose tobacco per day); smoking satisfaction (measured using the mCEQ).

• *Use of NRT: *All participants will be asked about use of any NRT (including type, dosage, flavour, and frequency of use) at every time point.

• *Use of non-NRT methods of cessation: *Participants will be asked about their use of non-NRT methods of cessation such as buproprion, clonidine, nortriptyline, varenicline, acupuncture etc, measured at two and six months only.

• *Alcohol use and abuse: *Measured using the AUDIT-C. Measured at one and two months only.

• *Adverse events: *Information regarding any adverse events and whether they are considered to be related to treatment will be collected at every time point.

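### The only adverse-event measure stated by arm is filtered on seriousness and suspected cause, although every adverse event is collected and the callers know the allocation

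*Protocol article*

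**What the plan says.** **What is collected.** Protocol article, Outcome measures, Secondary outcome, in the list of measures taken in all participants at one week and at one, two and six months: "Information regarding any adverse events and whether they are considered to be related to treatment will be collected at every time point".

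**What is analysed.** Data analysis, Tolerability, sets an analysis population and three analyses:

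- Population: "All randomised participants who receive at least one dose of intervention or control treatment will be included in the planned analyses".
- Withdrawal: "Comparison of the frequency of treatment withdrawal between the intervention and the control group will be tested using Chi-square statistics".
- Discontinuation: "The numbers of participants discontinuing treatment prematurely for any reason will be summarised by treatment group and by reasons for discontinuation".
- Events: "The incidence of all suspected serious adverse treatment reactions will be summarised by treatment group".

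**Who knows the allocation.** Blinding: "Due to the nature of the intervention only single blinding (of researchers, not of participants) is possible". The same section then makes an exception for the staff who make the follow-up calls: "The senior research manager and research assistants based at Quitline will not be blinded to treatment allocation". The project co-ordinator is also unblinded. The rest of the study team stays blinded until the last follow-up call has been recorded.

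**The concern.** The article names an outcome, any adverse event in anyone, and then commits to summarising a small part of it that is selected by judgement. An event must be classed as serious and be suspected to be a treatment reaction before it enters the stated by-arm event summary.

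The causality filter is the weaker of the two in this design. One arm receives the service's usual NRT. The other receives a product that the Background describes as coming from plants considered poisonous, and as rarely mentioned in English-language literature. Someone who knows the allocation may attribute the same event differently in the two arms, and the direction cannot be predicted.

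The seriousness filter loses information. The Background says that cytisine is well tolerated and resembles NRT in its adverse effects. This trial compares the two directly and gathers the data to examine that statement, but followed as written, the Tolerability section would leave most of the events out of the by-arm event summary. At stake is how far the safety results can be interpreted. The primary abstinence outcome is unaffected.

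**Working it through.** The plan gives no adverse-event rate and no calculation on this point, so there is no stated figure to reproduce. The check is a comparison of sections, followed by an illustration on assumed values.

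**Step 1. Collection against analysis.**

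| Type of event | Collected? | Stated by-arm summary in Tolerability? |
|---|---|---|
| Serious, suspected to be a reaction | Yes | Yes |
| Serious, not suspected | Yes | None, unless it leads to stopping |
| Non-serious, leads to stopping | Yes | Indirectly, through discontinuation by reason |
| Non-serious, does not lead to stopping | Yes | None |

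No other section of the article states a by-arm summary for the uncovered rows.

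**Step 2. Where knowledge of allocation enters.** Events and relatedness are collected at the scheduled follow-ups. The Blinding section explains that the Quitline research assistants must know the group in order to make those calls, and participants know it too. The account of each event therefore passes between two people who know the treatment. The relatedness judgement is worded in the passive, and nobody is named as making it. If a blinded person makes it later, that person still works from those accounts.

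**Step 3. How far the causality filter alone could move the summary.**

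Inputs:

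- n = 655 per arm (Sample size section). This is an upper limit, because the tolerability population requires at least one dose.
- r = proportion with a serious event, equal in both arms. Assumed, 2% to 5%.
- a1, a0 = proportion of those events attributed to treatment in each arm. Assumed.

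Formula: expected suspected count = n × r × a. With equal n and r, the ratio between arms is a1/a0, which depends on neither n nor r.

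All serious events per arm: 655 × 0.02 = 13.1, and 655 × 0.05 = 32.75.

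| r | a1 v a0 | Suspected counts | Ratio |
|---|---|---|---|
| 2% | 50% v 50% | 6.6 v 6.6 | 1.0 |
| 2% | 60% v 30% | 7.9 v 3.9 | 2.0 |
| 2% | 30% v 60% | 3.9 v 7.9 | 0.5 |
| 5% | 50% v 50% | 16.4 v 16.4 | 1.0 |
| 5% | 60% v 30% | 19.7 v 9.8 | 2.0 |
| 5% | 30% v 60% | 9.8 v 19.7 | 0.5 |

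In every row the all-cause counts are equal between arms (13.1 v 13.1, or 32.75 v 32.75). Any difference in the suspected counts comes from attribution alone. The same mechanism could also hide a true difference.

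**The case against.** The strongest reply is that this is a condensed article. It says that a statistical analysis plan specifies all analyses in advance, and adverse-event tables are commonly left to such a plan. The Tolerability section does not say that other events will go unsummarised. This stands to the extent that fuller tables may already be planned. It does not dispose of the point, because the article does fix one event measure and that measure suits neither the design nor the outcome that the article lists. If the unseen plan already has all-cause tables, only the article's sentence needs to be brought into line.

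The independent safety committee receives safety reports from the study statistician and may review any information. That is partial mitigation, since the content of the reports is not given.

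A reader might infer more than the document supports:

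- *That safety is compared only on suspected serious reactions.* Withdrawal is tested and discontinuation is summarised by reason. The reactions are to be summarised, with no test named.
- *That the trial is open-label and causality is judged unblinded.* The article describes a single-blind trial with most of the team blinded. The Withdrawal criteria section gives the principal investigator a judgement on serious events, and that role is not listed among the unblinded. Unblinded attribution is a plausible risk and not a stated fact.
- *That non-serious events are what drives early stopping, and that these are lost.* The article does not say what drives stopping, and discontinuation by reason would pick up non-serious events that lead to it.
- *That the safety comparison loses the protection of randomisation, or that low power for rare reactions is the defect.* The first goes too far: arms are still summarised as groups, and the problem is confined to one filter. The second would need event rates that the document does not give, for a test that it does not plan.

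**Conclusion.** The point holds in limited form. The article collects all adverse events with relatedness, but the only adverse-event measure it states by arm is suspected serious reactions. Because participants and callers know the allocation and the assessor of relatedness is not named, the causality filter may act differently in the two arms. Non-serious events that do not lead to stopping have no stated summary.

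The size cannot be taken from the document. On the assumed rates above, unequal attribution alone gives a twofold ratio in either direction. Equal attribution gives no distortion. The conclusion that the filter is a poor choice rests on the wording of the Secondary outcome, Blinding and Tolerability sections and not on those rates. It is a correctable weakness in the safety summary, subject to what the full analysis plan contains.

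**What to change.** In the Tolerability section, extend the event sentence along these lines:

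*All adverse events and all serious adverse events, regardless of attributed cause, will be summarised by randomised arm over the same time window, as the proportion of participants affected, with risk difference and 95% CI. Suspected serious reactions will be given as an additional summary.*

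The window should be fixed in advance and be the same in both arms, since the cytisine course lasts 25 days and the NRT course eight weeks. It would also help to name who judges relatedness and whether that person knows the allocation.

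The cost is a few extra tables from data already collected, with no new procedure. The change has a limit that should be stated with the results: participants who know their treatment would still be reporting events to callers who know it. The all-cause summaries remove attribution bias but not reporting bias, which is likely to matter most for non-serious events.

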### Ethics

Ethics approval has been granted by the National Multi-Regional Ethics Committee (Ethics number MEC/10/08/078). Maintenance of confidentiality and compliance with the Privacy Act will be emphasised to all study participants. Participation in the study is entirely voluntary. Verbal consent will be obtained at the time of contact with Quitline, however a written consent form and patient information sheet will be posted out to participants for their information. Data will be entered, stored and backed-up in a secure manner via the Unit's internet data management system. Participants will be acknowledged in all publications and presentation of the results, and will receive a copy of the trial findings written in lay terms.

## Discussion

### Primary outcome assessment

The non-inferiority trial design precludes us from having a primary outcome based on six month quit rates. Loss to follow up and treatment non-compliance tends to reduce observed differences in treatment effect, which in non-inferiority trials biases findings away from the null. Later assessments are more likely to suffer from loss to follow up and treatment non-compliance, particularly as participants in the intervention group may use NRT after they have completed their 28 day course of cytisine if they feel it necessary to support their on-going quit attempt. Removing these participants from per protocol analysis of six month quit rates is likely to significantly reduce the power of the study. Instead the primary outcome will be based on a one month assessment of quit rates, with six month quitting variables collected as secondary outcomes.

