#### Intervention

Participants in the intervention arm will receive a 25-day course of cytisine tablets (Tabex^®^) delivered by courier. Participants will be asked to reduce their smoking over the first four days of treatment so that they are not smoking at all by the fifth day, which will be their designated Quit date. Participants will follow the dosing regimen as recommended by the manufacturer, namely:

• Days 1-3: 1 tablet every 2 hours through the waking day (up to six tablets per day)

• Days 4-12: 1 tablet every 2.5 hours (up to 5 per day); designated Quit date is day 5

• Days 13-16: 1 tablet every 3 hours (up to 4 per day)

• Days 17-20: 1 tablet every 4-5 hours (3 per day)

• Days 21-25: 1 tablet every 6 hours (2 per day)

As part of an automated process at Quitline, all participants, including those in the treatment group, will be sent Quitcards, which may be redeemed for subsidised NRT (see below for more detail). However, participants will be asked to use the cytisine tablets sent to them for the first 25 days, and not the NRT. Participants will be told to redeem their vouchers for NRT only if they are smoking one month after their trial quit date or require on-going cessation support after they have finished the course of cytisine.

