### Sample size

A sample size of 1,310 (655 in each group) is required for this trial. Internal Quitline service evaluations and previous findings from a cessation trial conducted by the Clinical Trials Research Unit have established that the average four week quit rate in people receiving usual care through Quitline is approximately 50% [31,32]. A non-inferiority margin of difference between the group proportions was set at 5% (i.e. the quit rates in the cytisine treatment group will be no worse than 5% less than the rate in the NRT active control group). A sample size of 1,310 will be sufficient to confer 90% power at the one-sided significance level of 0.025 using a binomial test for equivalence. The true four week quit rate in those who receive cytisine was assumed to be 55%, which is midway between the estimated efficacy of varenicline (60%) [8] and NRT [6]. The required sample size incorporates a 20% inflation factor to allow for a sufficiently large dataset to evaluate the intervention based on both the intention to treat as well as the per protocol population. The sample size is adequately powered to also evaluate the non-inferiority of cytisine on two month quit rates. Recruitment will take approximately 18 months based on previously run Quitline trials [32,33], and will aim for a minimum of 25% of participants to be Māori and 15% to be Pacific peoples. The sample size will allow the consistency of effects for Māori and Pacific peoples compared to non-Māori non-Pacific to be assessed.

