A pre-analysis review will be conducted before the primary analyses. The purpose of this review is to establish rules for a per protocol analysis and to reconsider the analysis plan (e.g., adjustment for potential confounders) in light of recent research. Any amendments (and the rationale) will be justified and documented in the statistical analysis plan. A per protocol analysis involves looking at the major protocol violations such as cross-over treatments, withdrawals and lost to follow-up. The per protocol population will consist of all randomized patients who have complied with the treatment allocated, were not lost to follow-up, and who do not have major protocol deviations pertaining to eligibility or the assessment of the treatment difference.

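### NRT use that the protocol permits after the cytisine course is treated as non-compliance for the six-month per-protocol analysis; removing those users acts on one arm only and can bias the result, not merely cost power

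*Protocol article*

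**What the plan says.** Three parts of the protocol article bear on NRT use in the cytisine arm after the course.

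- **Study intervention, Intervention.** All participants are sent Quitcards. Cytisine participants are asked to use the tablets and not NRT during the 25 days. After that, "Participants will be told to redeem their vouchers for NRT only if they are smoking one month after their trial quit date", or if they need further support once the course is finished. There are thus two permitted routes to NRT: smoking at one month, and wanting more help after the course.
- **Discussion, Primary outcome assessment.** NRT use after the course is the example given of non-compliance at later assessments. The section continues: "Removing these participants from per protocol analysis of six month quit rates is likely to significantly reduce the power of the study". Power is the only cost of removal that it names.
- **Data analysis, Treatment effects.** "A per protocol analysis involves looking at the major protocol violations such as cross-over treatments, withdrawals and lost to follow-up". The per-protocol population must have complied with allocated treatment. The detailed rules are left to a pre-analysis review.

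Two other statements set the context. Sample size says "The sample size is adequately powered to also evaluate the non-inferiority of cytisine on two month quit rates". Treatment effects makes intention-to-treat primary, with those lost to follow-up counted as smoking, and says that the per-protocol results will be considered as well.

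**The concern.** A cytisine participant who redeems a voucher on either permitted route is doing what the protocol allows, yet the Discussion would take that person out of the six-month per-protocol analysis as non-compliant.

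The exclusion is not symmetrical. NRT is what the control arm was allocated, so this criterion cannot remove a control participant. It is also linked to outcome, because one of the two routes is defined by smoking at one month. Continuous abstinence allows at most five cigarettes from the Quit date. Most people on that route have already exceeded the limit, and no later NRT can undo this. Removing them takes known failures out of the cytisine denominator and leaves the matching control failures in.

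A per-protocol analysis sits beside intention-to-treat in a non-inferiority trial as a safeguard. Here its later result could depend on why people redeemed vouchers and not on how well cytisine worked.

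**Working it through.** **1. The plan's own figure.** The Sample size section gives rates of 50% (NRT) and 55% (cytisine), a 5-point margin, "90% power at the one-sided significance level of 0.025", and a 20% inflation.

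- n per arm = (1.960 + 1.282)² × (0.50×0.50 + 0.55×0.45) / (0.55 − 0.50 + 0.05)² = 522.7, so 523.
- 523 / (1 − 0.20) = 654 per arm, 1,308 in total, against 1,310 stated. The figure reproduces.
- The planned 655 per arm leaves 655 × 0.80 = 524 after the allowance. The checks below use 524.

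**2. The cost the Discussion names: power.** Suppose 20% of the cytisine arm is removed regardless of outcome, at the planned 55% and 50%. The standard error goes from 0.0308 to 0.0327. Power, Φ(0.10/SE − 1.96), goes from 90.1% to 86.4%. That is a modest loss.

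**3. The cost it does not name: bias.** Let p be the true cytisine rate, and let r_f and r_s be the shares of the cytisine arm removed as failures and as abstainers. The control arm is unchanged.

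Per-protocol cytisine rate = (p − r_s) / (1 − r_f − r_s)

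The NRT rate at the later time point is not in the documents; 45% is assumed. The removal shares are also assumed. The probability of declaring non-inferiority is Φ((difference + 0.05)/SE − 1.96), with 524 × (1 − r_f − r_s) cytisine and 524 control participants.

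| Removed from cytisine arm | Per-protocol rate if p = 45% | Difference (true 0) | Per-protocol rate if p = 40% | Difference (true −5) | Chance of declaring non-inferiority when truly at the margin |
|---|---|---|---|---|---|
| none | 45.0% | 0 | 40.0% | −5.0 | 2.5% |
| 5% failures | 0.45/0.95 = 47.4% | +2.4 | 0.40/0.95 = 42.1% | −2.9 | 10% |
| 10% failures | 0.45/0.90 = 50.0% | +5.0 | 0.40/0.90 = 44.4% | −0.6 | 29% |
| 15% failures | 0.45/0.85 = 52.9% | +7.9 | 0.40/0.85 = 47.1% | +2.1 | 59% |
| 10% failures, 5% abstainers | 0.40/0.85 = 47.1% | +2.1 | 0.35/0.85 = 41.2% | −3.8 | 5.6% |
| 10% failures, 10% abstainers | 0.35/0.80 = 43.75% | −1.3 | 0.30/0.80 = 37.5% | −7.5 | 0.3% |

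**4. Sensitivity to the assumed rates.** Take 50% (NRT) and 45% (cytisine), exactly at the margin, with 655 per arm. Removing 10% or 20% of the failures alone raises the false non-inferiority rate from 2.5% to 15% or 50%. Removing 20% of failures and 20% of abstainers leaves it at 2.5%. Removing 10% of failures and 20% of abstainers lowers it to 0.1%.

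The pattern does not depend on the assumed rates. The bias favours cytisine when failures are removed at a higher rate than abstainers, vanishes when the two rates are equal, and reverses when abstainers are removed at the higher rate.

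**The case against.** The case on the other side has real weight.

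- **No rule is fixed.** The Discussion sentence is design rationale, explaining why six months was not chosen as the primary time point. The rules are to be set at the pre-analysis review, and someone who finished the course and then took permitted NRT could be read there as compliant. This stands, so the point concerns what the review must settle and not an error already built in. The Discussion is nevertheless the only place that says how these people would be handled, and it says removal.
- **Two months is not mentioned.** The Discussion names six months only. The two-month case is inferred from the planned two-month non-inferiority evaluation and the listing of cross-over treatments as a violation. This stands.
- **The direction is unknown.** The second route covers people who are still abstinent, and the Discussion itself refers to NRT supporting a continuing quit attempt. A reader might infer that the later per-protocol sets are certain to favour cytisine, by about the margin. The documents do not support that: they give neither how many redeem nor why, and the bias can vanish or reverse.
- **The whole set is not one-sided.** Loss to follow-up, non-compliance and eligibility deviations apply to both arms. Only the NRT criterion acts on cytisine alone.
- **Keeping everyone has a cost.** Retaining abstainers who then use the comparator can dilute the contrast, which is the Discussion's own worry. This stands for abstainers. It does not apply to people who had already failed continuous abstinence, because NRT cannot change their result. For seven-day point prevalence, also measured at every time point, NRT could change the result, so the argument is confined to continuous abstinence.

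**Conclusion.** The point holds in a limited form. The Intervention section and the Discussion classify the same NRT use differently. The removal described would act on the cytisine arm only, and the Discussion names only the lesser cost. Removal unrelated to outcome costs little power (90.1% to 86.4% for 20% of the arm). Removal of failures alone, equal to 5% to 15% of the arm, would shift the difference by +2.4 to +7.9 points and raise false non-inferiority at the margin from 2.5% to between 10% and 59%. With 10% failures and 10% abstainers removed, the shift is −1.3 points.

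These sizes rest on an assumed 45% later rate, assumed removal shares and a normal approximation; the actual size and sign cannot be known from the documents. The reach is secondary: per-protocol analyses at six months, and by inference at two. A reader might take this as a threat to the trial's main conclusion. It is not, because the primary one-month intention-to-treat analysis removes nobody for NRT use. The point is worth settling because the per-protocol result is meant to be weighed alongside intention-to-treat.

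**What to change.** Reconcile the Intervention section, the per-protocol text under Treatment effects and the Discussion when the per-protocol rules are set, before unblinding. For continuous abstinence at two and six months:

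1. Anyone who exceeded five cigarettes since the Quit date before starting permitted NRT stays in the per-protocol set as a failure.
2. For participants still abstinent when they start permitted NRT, report the later per-protocol result both with and without them. Label the version that keeps them as cytisine followed by permitted NRT.
3. Show post-course NRT use by arm beside these results.

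The two sections also give different course lengths (25 days under Intervention, 28 days in the Discussion). These must be reconciled too, since the end of the course determines when NRT use counts as post-course.

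The cost is a few sentences in the per-protocol rules and one more secondary analysis. NRT use is already asked at every time point. What participants are told need not change.
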